## Abstract

**Background:**

Shoulder pain is the third most common musculoskeletal disorder, often affecting people’s daily living and work capacity. The most common shoulder disorder is the subacromial impingement syndrome (SIS) which, among other pathophysiological changes, is often characterised by rotator cuff tendinopathy. Exercise is often considered the primary treatment option for rotator cuff tendinopathy, but there is no consensus on which exercise strategy is the most effective. As eccentric and high-load strength training have been shown to have a positive effect on patella and Achilles tendinopathy, the aim of this trial is to compare the efficacy of progressive high-load exercises with traditional low-load exercises in patients with rotator cuff tendinopathy.

**Methods/Design:**

The current study is a randomised, participant- and assessor-blinded, controlled multicentre trial. A total of 260 patients with rotator cuff tendinopathy will be recruited from three outpatient shoulder departments in Denmark, and randomised to either 12 weeks of progressive high-load strength training or to general low-load exercises. Patients will receive six individually guided exercise sessions with a physiotherapist and perform home-based exercises three times a week. The primary outcome measure will be change from baseline to 12 weeks in the patient-reported outcome Disabilities of the Arm, Shoulder and Hand (DASH) questionnaire.

**Discussion:**

Previous studies of exercise treatment for SIS have not differentiated between subgroups of SIS and have often had methodological flaws, making it difficult to specifically design target treatment for patients diagnosed with SIS. Therefore, it was considered important to focus on a subgroup such as tendinopathy, with a specific tailored intervention strategy based on evidence from other regions of the body, and to clearly describe the intervention in a methodologically strong study.

**Trial registration:**

The trial was registered with Clinicaltrials.gov (NCT01984203) on 31 October 2013.

## Background

People with pain in the neck and shoulder region are often disabled to the point where they cannot live a normal life. The pain may also influence the person’s work capacity and financial as well as social situation. Pain in the shoulder is the third most common musculoskeletal disorder, and the lifetime prevalence is estimated to be between seven and 10% [1]. The prevalence for daily non-specific shoulder pain in a normal working population in an industrialised country is estimated to be 12% [2]. Furthermore, up to 23% of the workforce seeking care from the healthcare system with a shoulder problem have been sick-listed for more than one week [3].

Clinically, the most common shoulder-related cause of contact with the healthcare system is subacromial impingement syndrome (SIS), which accounts for 33% of all shoulder-related healthcare contact [4,5]. SIS is generally considered to be a cluster of symptoms, rather than a single pathology. The Complaints of the Arm, Neck and/or Shoulder (CANS) model defines SIS as ‘Disorders that include the rotator cuff syndrome, tendonitis of the m. infraspinatus, m. supraspinatus and m. subscapularis, and bursitis in the shoulder area’ [6]. The cause of SIS is considered to be multi-factorial and involves an altered muscle recruitment pattern in the rotator cuff and thoracoscapular muscles, potentially in combination with alterations to the anatomical structures in the subacromial space. These alterations may result in varying degrees of micro-traumas and degenerative pathophysiological changes in the rotator cuff muscle and surrounding tissue, which eventually can result in rotator cuff tendinopathy. Generally, the clinically relevant pathophysiological conditions associated with the diagnosis of SIS, such as rotator cuff tendinopathy, are often difficult to identify objectively [7,8], and consequently the diagnosis of rotator cuff tendinopathy is primarily based on a combination of the patient’s history, clinical tests and ultrasonographic visualisation of changes in the rotator cuff tendons.

The Danish national clinical guidelines for the treatment of SIS recommend active rehabilitation strategies, and in cases where three to six months of exercise has been ineffective, arthroscopic subacromial decompression surgery can be considered [9]. These recommendations are, amongst others, based on the evidence that exercise has shown results comparable to arthroscopic subacromial decompression when evaluated on pain and patient-reported function [10-14]. However, the recommended guidelines rarely describe specific exercise programmes, nor are they sufficient in detail to be targeted at subgroups of SIS, such as rotator cuff tendinopathy. This means there is no consensus on specific rehabilitation exercise programmes for SIS patients with rotator cuff tendinopathy.

Among patients with Achilles or patella tendinopathy, studies of eccentric or progressive high-load exercises have shown promising effects on pain and function [15], and such exercises for chronic tendinopathy are often considered to be the first line of treatment [16-18]. Some of the mechanisms believed to be responsible for the positive outcomes of eccentric exercises are reduced structural abnormalities, such as hypoechoic areas, irregular structures, neovascularisation and tendon thickness [19,20]. The reasons for these changes could possibly be increased collagen type I synthesis [21]. Considering that collagen synthesis peaks at between 24 and 72 hours post-exercise [22], programmes prescribing daily training, such as those recommended for standard eccentric exercise programs, might not be optimal [23]. In support of this, very high-load eccentric training with relatively few repetitions and low frequency (twice a week) has shown equally beneficial effects on patella tendinopathy [24,25]. Also, concentric heavy slow resistance exercises, without emphasis on the eccentric component, three times a week [25] has shown positive effects on patella tendinopathy. Furthermore, heavy slow resistance exercises seem to reduce abnormal fibrillar morphology among patients with patella tendinopathy [26].

However, rotator cuff tendinopathy is often treated as any other subgroup of SIS, with a combination of low-load exercises for internal and external rotation of the shoulder joint, with an attempt to target the rotator cuff muscles and optimise muscle coordination. Only a few studies have used progressive exercises or eccentric exercises in patients with SIS, and they have reported positive results on pain and function [27-32]. But all these studies have primarily targeted SIS and did not differentiate between the underlying pathologies. Inclusion of different subgroups of SIS in the same trial makes it difficult to customise an optimal exercise programme and, possibly, to detect a clinically relevant change between different exercise strategies [8].

Based on the evidence reported from studies on knee, Achilles and elbow tendons, applying eccentric or high-load exercise programmes in patients with rotator cuff tendinopathy could be beneficial for patients’ pain, function and quality of life [8], and for ultrasonographic visualised structural changes [33-35], when compared with traditional exercise strategies. But the rationale for using progressive high-load exercises is the diagnosis of tendinopathy and therefore, unlike existing studies, a study of eccentric or progressive high-load exercises should include only patients with tendinopathy. To our knowledge, no studies have investigated the effect on pain and function of progressive high-load exercises compared with traditional low-load exercises in the subgroup of SIS patients primarily showing signs of rotator cuff tendinopathy. A proportion of patients diagnosed with tendinopathy will also have a concomitant pathology in the surrounding tissue of the glenohumeral joint. Often corticosteroid injection into the subacromial space is used as an adjunct treatment for exercise interventions, if regarded relevant by the orthopaedic specialist. It is uncertain if this concomitant treatment has an additional effect on the exercise treatment.

The aim of the study is to determine in a randomised, double-blind controlled trial if a progressive high-load exercise programme for the rotator cuff muscles is superior to a traditional low-load exercise programme in patients with rotator cuff tendinopathy, based on the primary endpoint; change in score on the Disabilities of the Arm, Shoulder and Hand (DASH) questionnaire [36] after 12 weeks of exercise. The second aim is to evaluate the possible interaction of concomitant use of corticosteroids with the exercise intervention.

## Methods/Design

### Study design

This trial, called the Rotator Cuff Tendinopathy Exercise (RoCTEx) trial, is a multicentre (three sites), stratified (by corticosteroid injection (yes or no)), randomised, controlled, observer- and patient-blinded superiority trial, with a two-group parallel design, to be conducted in Denmark. The primary endpoint will be 12 weeks after baseline. Patients will be randomised to either progressive high-load exercises or low-load exercises (block randomisation with a 1:1 allocation). As illustrated in Figure 1, patients will also be assessed at one year from the baseline, referred to as the follow-up assessment.

**Figure 1 Fig1:**
[figure not shown]
**Expected flow of participants through the study.** LLE: low-load exercises; PHLE: Progressive high-load exercises.

### Settings and locations

Patients will be recruited from the shoulder units at the outpatient clinics of orthopaedic departments at the Hospital Lillebaelt - Vejle Hospital, Aalborg University Hospital - Farsø Hospital and Odense University Hospital - Svendborg Hospital.

### Participants

The orthopaedic specialists will perform a standardized initial screening of all patients referred to the shoulder units. If patients fulfil the eligibility criteria they will be referred to the principal investigator, who will perform the final eligibility assessment and give detailed information about the study. Patients will be invited to participate if they meet the following inclusion criteria: between 18 and 65 years of age, have a current shoulder complaint lasting at least three months prior to the time of enrolment, pain is located in the proximal lateral aspect of the upper arm (C5 dermatome) that is aggravated by abduction, a positive ‘Full Can Test’ and/or Jobe’s test and/or Resisted External Rotation Test, a positive Hawkins-Kennedy test and/or Neer’s test, ultrasonographic verification of either tendon swelling, and/or presence of hypoechoic areas, calcification, fibrillar disruption and/or neovascularisation in the m. supraspinatus.

Patients will be excluded if they fulfil any of the following exclusion criteria: Resting pain more than 40 mm on a visual analogue pain scale (range: 0 to 100), bilateral shoulder pain, less than 90 degrees of active elevation of the arm, a full thickness rupture in the rotator cuff tendon verified by ultrasonography, presence of calcification larger than 5 mm (vertical distance) verified by x-ray, corticosteroid injection within the last six weeks, a radiologically verified fracture, glenohumeral osteoarthritis, prior surgery or dislocation of the affected shoulder, a clinically suspected labrum lesion, symptomatic arthritis in the acromioclavicular joint, a frozen shoulder or symptoms derived from the cervical spine, sensory or motor deficit in the neck or arm, suspected competing diagnoses (for example, rheumatoid arthritis, cancer, neurological disorders, fibromyalgia, psychiatric illness), pregnancy or inability to understand spoken and written Danish.

### Interventions

Generally, both groups will receive the same exercises (although they differ on the amount of load), attention and basic information about ergonomic corrections related to the daily use of the upper extremity. The exercise program will consist of six exercises: two exercises for the scapula stabilising muscles (push-up plus exercise and low row exercise), two for the rotator cuff muscles (scaption and side-lying external rotation), and two stretching and mobility exercises (posterior capsule stretch and scapulae retraction). Patients will be instructed in performing home-based training three times per week, and will be seen for initial instruction in week one (60 minutes), and follow-up exercise sessions (30 minutes) in weeks two, three, four, six and nine. The general information about the project and exercise instructions will be given through a DVD to minimise the influence of the physiotherapist. On the first visit to the physiotherapist, the patients will receive detailed instructions on how to perform the exercise programme based on the instructions on the DVD. At the follow-up exercise sessions corrections will be made, and weights adjusted. The patients will be given a copy of the DVD and an exercise brochure to enable them to follow the instructions and exercises at home.

The difference between the intervention and control groups will be the external load targeting exercises for the rotator cuff. The intervention group will perform 12 weeks of progressive high-load exercises, gradually increasing the load from 15 repetitions maximum (RM) in week one to six RM in weeks nine to 12. The intervention group will only be allowed to do isometric exercises if the pain exceeds 50 mm on the visual analogue scale. The control group will perform 12 weeks of low-load exercises, performed with 20 RM from weeks one to 12. For both groups, scapulae exercises will be performed with 20 RM, and stretching and mobility exercises will be performed five times, for 20 seconds each, in weeks one to 12.

Concomitant use of corticosteroid injections will be based on the orthopaedic specialist’s evaluation, in accordance with the department’s standard procedures. Between 25 and 50% of patients are expected to receive injections. The corticosteroid injections will be given to patients at the shoulder unit of the orthopaedic departments, after baseline assessment but before randomisation. Randomisation will be performed in a stratified manner to ensure even distribution of patients receiving and not receiving corticosteroid injections in the two exercise groups.

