### Sample size and power considerations

Studies on patients with SIS have shown mean baseline values for DASH scores between 18 and 65, and standard deviations (SD) between 12 and 20 [30,31,43-47]. Often a 50% reduction in DASH score is seen after treatment [30,31,44,46,47], and it is suggested that a 40% change corresponds to a substantial improvement for the patient [46]. Based on these data, we expect a mean baseline of 40 points on the DASH questionnaire with an SD of 17. We expect a 50% change (change from 40 to 20 DASH points) in the progressive high-load exercise group, and 25% (change from 40 to 30 DASH points) in the low-load exercise group (Figure 2A).

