### Randomisation and allocation concealment

Patients will be randomly assigned to either of the two exercise groups with a 1:1 allocation as per a computer-generated randomisation schedule, stratified by administration of concomitant corticosteroid injection using permuted blocks of random sizes (two to six). The primary investigator, assessors and administrator of the randomisation procedure will not know block sizes in order to ensure allocation concealment. In practice, after recruitment and baseline measurements, the secretary at the physiotherapy department will administer the allocation procedure by taking a sequentially numbered, opaque sealed envelope from one of two ring binders, determined by the potential referral to corticosteroids (yes or no) by the orthopaedic specialist.

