### Statistical analysis plan

The primary efficacy analysis performed is assessment of the between-group difference in change in the DASH score after 12 weeks in the intent-to-treat (ITT) population (all randomised patients independent of compliance and withdrawals). In the case of missing data due to drop-outs, a non-responder imputation will be applied; a baseline observation carried forward (BOCF) technique will be used for patients who do not complete the study (as will be illustrated in a corresponding trial flow diagram).

For the primary analyses at week 12, we will use analysis of covariance (ANCOVA) to compare the progressive high-load exercise group with the low-load exercise group for mean changes from baseline in the DASH score, as well as the secondary continuous outcomes. The primary model includes the change from baseline as the dependent variable, with treatment group (progressive high-load exercise or low-load exercise), corticosteroid status (yes or no), and the centre site (one, two or three) as main effects, with the baseline score as an additional covariate. The secondary analysis for the primary outcome will add the interaction term for group × corticosteroid in the primary model.

To analyse the longitudinal element of time effects of DASH in the randomised trial (repeated measures design three, six, nine, and 12 weeks), a linear approach will be used, fitted in SAS software (version 9.3 Service Pack 4; SAS Institute Inc., Cary, North Carolina, United States) using the procedure ‘PROC MIXED’ based on restricted maximum likelihood (REML) estimates of the parameters. The variable ‘patient’ will be applied as a random effects factor. Assessment of the treatment and time effects is of exploratory interest for the primary outcome in testing for a possible interaction, and both treatment and time will be used as systematic factors, using the baseline value as covariate to reduce random variation and increase power.

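### Injection is chosen by the clinician, so the second aim can show whether the exercise effect differs between patients selected and not selected for injection, but not that the injection causes the difference

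*Protocol article*

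**What the plan says.** The Background sets the aim: "The second aim is to evaluate the possible interaction of concomitant use of corticosteroids with the exercise intervention". It introduces this by noting uncertainty about whether the concomitant injection adds to the effect of exercise.

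Under Interventions, the decision to inject is clinical: "Concomitant use of corticosteroid injections will be based on the orthopaedic specialist’s evaluation, in accordance with the department’s standard procedures". The injection is given "after baseline assessment but before randomisation", and the expected uptake is a range: "Between 25 and 50% of patients are expected to receive injections". Study design describes a trial that "is a multicentre (three sites), stratified (by corticosteroid injection (yes or no)), randomised". Exercise is thus randomised within injection strata, and injection itself is not randomised.

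Under Statistical analysis plan, the primary ANCOVA has exercise group, corticosteroid status and centre as main effects, with baseline score as a covariate. For the second aim: "The secondary analysis for the primary outcome will add the interaction term for group × corticosteroid in the primary model". No group × baseline or group × centre term is named.

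Under Sample size and power considerations, the second objective is sized on a different quantity: injected versus non-injected patients inside the high-load arm, 10 DASH points apart, SD 17, 62 per stratum for 90% power. The article nowhere says that this comparison is non-randomised or that the interaction is associational.

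**The concern.** Patients picked for injection by a specialist, under the routines of three departments, may differ from the others in severity and site. Stratified randomisation makes the exercise arms comparable within each stratum. It does not make the two strata comparable with each other.

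Two quantities are affected, to different degrees. The interaction term is distorted only if the exercise effect itself varies with something that differs between strata. The injected versus non-injected contrast within the high-load arm is distorted by any prognostic difference between the strata. At stake is a statement that the injection enhances or blunts high-load exercise when the real modifier, or the real prognostic factor, is severity or site. The primary comparison of the two exercise programmes is not affected.

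**Working it through.** **1. The plan's own figures.** With a difference of 10, SD 17 and two-sided 0.05, the noncentral t gives power 0.901 at 62 per stratum and 0.897 at 61, so the stated 62 is right. For the primary outcome, 100 per group gives 0.985, as stated. The sample-size arithmetic is not in dispute.

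**2. What cancels.** Write the mean change in stratum k as m_k in the low-load arm and m_k + D_k in the high-load arm.
- Interaction = D_1 − D_0. The prognostic terms m_1 and m_0 drop out.
- Injected minus non-injected within the high-load arm = (m_1 − m_0) + (D_1 − D_0). The prognostic gap stays in.

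**3. Size of a false interaction, as an illustration.** The sample-size section says: "We expect a 50% change (change from 40 to 20 DASH points) in the progressive high-load exercise group", and 40 to 30 (25%) in the low-load group. Assume that these percentages hold at every baseline level. The exercise effect is then (0.50 − 0.25) × baseline. A single common baseline slope averages over the arms and leaves D_1 − D_0 untouched. The documents give no baseline by injection status, so the gaps are assumed:
- gap 10 (45 versus 35): 11.25 − 8.75 = 2.5 points;
- gap 20 (50 versus 30): 12.5 − 7.5 = 5 points.

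**4. Rejection rate when corticosteroid modifies nothing.** Use SD 17 and 260 patients.
- 50% injected (65 per cell): SE = 17 × √(4/65) = 4.22.
- 25% injected (cells 97, 97, 33, 33): SE = 17 × √(2/97 + 2/33) = 4.84.

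Rate = Φ(−1.96 + bias/SE) + Φ(−1.96 − bias/SE):

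| Assumed gap | Bias | 50% injected | 25% injected |
|---|---|---|---|
| 0 | 0 | 5% | 5% |
| 10 | 2.5 | 9.1% | 8.1% |
| 20 | 5 | 22.0% | 17.8% |

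Simulating the ANCOVA under the same assumptions (without centre) gave 2.6 and 5.1 points at 50% injected, with rejection about 8% and 22%. Adding group × baseline brought the estimate back to about 0 and rejection to 5–6%.

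**5. Simulation of the stated model with centre.** N = 260, three centres, injection more likely with severity and differing by centre, true injection effect zero. All effect sizes are assumed.
- Severity and centre act equally in both arms: interaction 0.1 points.
- Exercise effect varies by centre (5 points per step): 2.7. By severity (5 points per SD): 3.9. By both: 6.3.
- Within-high-load contrast with no effect modification: 7.7 points unadjusted, and 5.2 from the model with centre and baseline DASH, because baseline DASH was set to capture severity only in part. The comparison figure is the hypothesised 10.
- If only centre drives prognosis, the adjusted within-high-load contrast is about 0 and the unadjusted one is 1.6.

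**6. Precision cost of a group × baseline term, equal strata.** SE ratio = √(1 + (gap/2)²/s²), where s is the within-stratum baseline SD. Take s² = 17² = 289, or s² = 289 − (gap/2)² if 17 is the overall SD.
- Gap 10: √(1 + 25/289) = 1.04; √(1 + 25/264) = 1.05.
- Gap 20: √(1 + 100/289) = 1.16; √(1 + 100/189) = 1.24.

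Group × centre would add to this if injection habits differ by site.

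**The case against.** The strongest defence is that the planned interaction is already well protected. Exercise is randomised within injection strata, and centre and baseline score are in the model. A reader might infer that the term simply credits severity and centre differences to the injection. The documents do not support that: differences acting equally in both arms cancel (0.1 points in step 5). This part of the defence stands in full.

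Second, the proportional effect is an inference. The sample-size section gives one group-mean scenario at a baseline of 40 and powers on a fixed 10-point difference. It states no patient-level slope. A reader might take the 50% and 25% as the protocol's commitment to an effect that scales with baseline, but they are not. The stratum gaps are also assumed. A 20-point gap with overall SD 17 is 20/√189 ≈ 1.45 within-stratum SDs, which is extreme, particularly when patients with resting pain above 40 mm are excluded. This stands too, so steps 3 and 4 are illustrations only.

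Third, the aim is secondary and is described as exploring a possible interaction, and companion models are often left to an analysis plan that is not shown here. The absence of such a model is therefore not itself an error. What remains is the article's own wording. It frames the aim as an interaction with corticosteroid use and sizes it on a non-randomised contrast, without limiting what can be concluded.

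**Conclusion.** The point holds in a limited form. The group × corticosteroid term is a valid answer to whether the exercise effect differs between patients selected and not selected for injection. It does not identify the injection as the cause. For the term to mislead, two things must both be true: the exercise effect varies with severity or centre, and injection is associated with that factor. Under the assumed proportional effect and a 10-point stratum gap, the false interaction is 2.5 points and the rejection rate is about 9% (about 8% with 25% injected) instead of 5%. The 20-point case marks an extreme.

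The within-high-load contrast is the weaker of the two, because it needs no effect modification to be biased. Its simulated bias of 5.2 to 7.7 points depends on assumed effects and shows only that confounding by indication could be material beside the hypothesised 10.

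This is an inexpensive improvement to a secondary aim. It neither undermines the primary analysis nor invalidates the planned interaction test.

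**What to change.** - **Background (second aim) and Sample size and power considerations:** restate the aim as whether the exercise effect differs between patients selected and not selected for injection. State that injected versus non-injected differences within an exercise arm are non-randomised and will not be read as an effect of the injection.
- **Statistical analysis plan:** keep the planned group × corticosteroid model. Add a pre-specified companion (sensitivity) model that also contains group × baseline DASH and group × centre, and read the two together.

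No new data are needed, since baseline DASH, centre and injection status are already in the primary model, and nothing about the clinical use of injections changes. The cost is precision in the companion: the group × baseline term raises the SE by a few percent at a 10-point stratum gap and by roughly 16–24% at a 20-point gap, with more lost to group × centre if sites inject at different rates. For that reason it should accompany the planned model and not replace it. Because baseline DASH captures severity only in part, the companion cannot make the result causal, and the rewording of the aim matters more.
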